### 2.7. Sample Size

The previous literature will serve as a guide for calculating sample size, based on the effect of the prescribed antibiotics and pharmacist-led educational interventions on successful adherence to therapy [31,32]. A sample size of the responses will be required to give a 95% confidence interval with a 5% margin of error. Therefore, the maximum number patients from each pharmacy will be recruited until the study sample size surpasses both groups (control and interventions). Once the sample size is achieved, the principal investigator and team members will halt the patient recruitment. We will aim to achieve a 1:1 allocation ratio in the intervention or control groups, with 80%’ power and an alpha error of 5%. For the dropout participants, a 20% attrition rate will be supposed, resulting in a minimum sample size of 400 (200 in each group).

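### Section 2.7 justifies 400 patients by a one-sample 5% margin that does not fit a two-arm comparison and is not met for it, and states 80% power without an effect size

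*Protocol article*

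**What the plan says.** Section 2.7 (Sample Size) gives two criteria in one paragraph.

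- Precision: "A sample size of the responses will be required to give a 95% confidence interval with a 5% margin of error"%. It does not say whether the margin applies to the whole sample, to each arm or to the difference between arms. No expected proportion is given.
- Power: "We will aim to achieve a 1:1 allocation ratio in the intervention or control groups", "with 80%’ power and an alpha error of 5"%. No control rate, difference, standard deviation or sidedness is given. The only source is a pointer to two references on adherence: "The previous literature will serve as a guide for calculating sample size".

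It then states the result: "For the dropout participants, a 20% attrition rate will be supposed, resulting in a minimum sample size of 400 (200 in each group"). It does not say which criterion produced the number.

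Three other parts of the article bear on this. Section 2.2 describes a two-arm trial with individual randomisation. Sections 2.14.1 and 2.14.2 make the BMQ and PAS-QA questionnaires primary and adherence secondary. Section 2.17 analyses the primary endpoint by mean differences between arms.

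**The concern.** A 95% interval with a 5% margin is the criterion for estimating one proportion in one sample, as in a survey. This trial exists to compare two arms. A margin on a pooled proportion says nothing about how precisely a difference is estimated, and a margin in percentage points is not defined for questionnaire scores analysed as mean differences.

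The power statement is the right kind of criterion for this design, but it has no alternative attached. A reader cannot tell what size of benefit the trial was planned to find, and may take the 5% margin as the precision of the treatment comparison. At stake is an accurate account of what 400 patients can show. The number itself need not change.

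**Working it through.** **Inputs from Section 2.7:** 95% confidence, 5% margin, 80% power, 5% alpha, 1:1 allocation, 20% attrition, 400 enrolled.

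**Assumptions, not in the document:** two-sided alpha; a proportion p, shown over a range; individual randomisation; no finite-population correction unless stated.

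**1. Can 400 be reproduced?** Not from the stated inputs, since neither p nor an effect size is given. For a pooled proportion, n = 1.96² × p(1 − p) / 0.05², divided by 0.8 for attrition and rounded up at each step:

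| p | Completers needed | Enrolled needed | Margin with 320 completers |
|---|---|---|---|
| 0.5 | 385 | 482 | 5.48 points |
| 0.7 (or 0.3) | 323 | 404 | 5.02 points |
| 0.8 | 246 | 308 | 4.38 points |

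Exactly 320 completers meet 5 points at p = 0.296 or 0.704. Whether 400 meets the pooled margin therefore depends on a p that the text does not state.

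**2. The margin for a two-arm trial.** Completers: 400 × 0.8 = 320, or 160 per arm.

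- One arm: 1.96 × √(p(1 − p)/160). At p = 0.5 this is 7.7 points; at 0.3 or 0.7 it is 7.1; at 0.8 it is 6.2.
- Difference, similar rates in both arms: 1.96 × √(2p(1 − p)/160). At p = 0.5 this is 11.0 points; at 0.3 or 0.7 it is 10.0; at 0.8 it is 8.8.

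Solving for the rates at which 5 points is reached:

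- One arm: p(1 − p) = 160 × (0.05/1.96)² = 0.104, so p is at most 11.8% or at least 88.2%.
- Difference: p(1 − p) = 80 × (0.05/1.96)² = 0.052, so p is at most about 5.5% or at least about 94.5%.

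This step does not depend on choosing p = 0.5.

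**3. What 160 evaluable per arm can detect with 80% power, two-sided 5%.**

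- Mean of a score, one unadjusted comparison: (1.96 + 0.8416) × √(2/160) = 0.313 SD.
- Two proportions, normal approximation without continuity correction:

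| Assumed control rate | Smallest difference with 80% power |
|---|---|
| 30% | 15.2 points |
| 40% | 15.6 points |
| 50% | 15.5 points |
| 60% | 14.7 points |
| 70% | 13.3 points |

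Check at 50% against 65.5%, with mean rate 0.5775: [1.96 × √(2 × 0.5775 × 0.4225) + 0.8416 × √(0.5 × 0.5 + 0.655 × 0.345)]² / 0.155² = 158.2, so 159 per arm, and 159/0.8 gives 199 enrolled per arm. So 400 is compatible with 80% power for an effect of this size. For 50% against 60% the power is 44%.

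**4. Unit of randomisation.** Section 2.4 splits pharmacies five and five, and Section 2.9 also randomises ten pharmacists. If these are the randomised units, 320/10 = 32 completers fall in each, and variance is multiplied by 1 + 31 × ICC. The document gives no ICC, so no figure is attached, but any positive ICC makes the results in step 3 less favourable.

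**The case against.** The strongest opposing case is that inputs are missing and nothing has been shown to be wrong. Much of that stands, and it rules out several readings that a reader might infer.

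- *That 400 is an arithmetic slip for about 480.* This needs p = 0.5. Section 2.7 points to literature on adherence, so a literature-based proportion is at least as natural. Near 0.7 the calculation gives 404 enrolled, and at 0.8 only 308. A finite-population correction could also bring the figure down. At p = 0.5 an eligible population of up to about 1,910 needs no more than 320 completers. Section 2.3 gives 2,000 to 10,000 residents per union council for two councils, but the eligible patients in Section 2.8 are a far narrower group of unstated size.
- *That 400 is 1/0.05² with attrition forgotten.* The match is exact, but nothing in the document shows that this formula was used.
- *That the 80% power is false.* Leaving the effect size unstated makes it impossible to check, not untrue, and step 3 shows effects for which it holds. The detail may lie in the cited references or a fuller protocol.
- *That a null result could not be interpreted.* The confidence interval for the difference would still be informative.

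The objection does not reach the comparison between arms. Both routes that bring the figure close to 400 work only for one proportion pooled over both arms. No single literature value between 5.5% and 94.5% gives a 5-point margin for the difference, and a fuller protocol would not turn a one-sample margin into a justification for two arms.

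**Conclusion.** The point holds in a limited form. The one-sample margin is the wrong criterion for this design, and 400 enrolled with 20% attrition does not meet it for the comparison. The half-width for the difference is 10.0 to 11.0 points at rates of 30 to 70%, about twice the stated figure. The exceptions are rates of about 5.5% or less, or 94.5% or more, in both arms. Such rates are unlikely for adherence in a trial whose inclusion criteria (Section 2.8) list poor adherence.

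The pooled shortfall (5.48 points at p = 0.5) is conditional and should be reported as such. The power statement is unverifiable, not refuted.

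These results rest on 160 evaluable patients per arm, two-sided 5% alpha, individual randomisation and similar rates in the two arms for the half-widths. The 0.31 SD figure ignores any gain from the baseline covariates in the Section 2.17 mixed model.

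**What to change.** Keep 400 and rewrite the paragraph in Section 2.7.

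1. Delete the sentence on the 5% margin.
2. State that 400 enrolled with 20% attrition leaves 320 evaluable, 160 per arm.
3. Name the endpoint that the number sizes. Section 2.7 refers to adherence, which Section 2.14.2 makes secondary, while Section 2.14.1 makes the questionnaires primary.
4. State the detectable effect at 80% power and two-sided 5% under individual randomisation: about 0.31 SD on the primary BMQ or PAS-QA score, and about 13 to 16 percentage points on the secondary adherence composite for control rates of 30 to 70% (15.5 points at 50%). Label the control rate as an assumption, or replace it with the rate from the cited literature and recompute.
5. If pharmacists or pharmacies are the randomised unit, state the ICC assumed and the lower power that follows.

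The cost is one paragraph and no extra patients. The downside is that the stated figures become less favourable than a 5% margin suggests.

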### 2.8. Recruitment of the Participants

#### Inclusion Criteria

Once their complete consent has been given, patients diagnosed with LRTIs (Table 1) will be screened for the inclusion criteria at the pharmacy. Poor adherence to recommended antibiotics for LRTIs, adult patient family members (age > 18 years), irrespective of gender, living in the UC for the last 1 year, and ability to speak and comprehend Urdu/Pushto or English are among the study’s qualifying requirements. Participants in the study group should have no extra comorbidities and have not participated in or been a part of any study/trial related to respiratory tract infections or antibiotics in the previous four months. Those who are unable to independently answer the questions owing to sight/vision, hearing, or cognitive problems, as well as those who do not meet the inclusion criteria, will be excluded (Figure 1).

### 2.9. Randomization

Using a computer-generated random digit number, a biostatistician will construct a random allocation order that is independent of/blinded to participants and trial size. For every participant that is recruited, a sample 1:1 is used to allocate them into control and interventional groups. Finally, ten pharmacists will be randomized to the intervention and control arms 1:1 and the permuted method will be used. This will be accomplished by the study teams exchanging a list of pharmacists, each of whom has a unique number assigned to them. The status of allocation will be conveyed to the research team coordinators, who will notify individual pharmacists as soon as the participants’ agreement to trial participation is obtained by research teams.

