## Abstract

Globally, lower respiratory infections (LRTIs) are one of the most common infectious diseases whichaffect majority of the population and as a result of inappropriate antibiotics practices lead to antibiotic resistance (AR). An individual randomized control trial will be conducted in the post-conflict areas of Swat, Pakistan, through a random sampling method. Patients aged > 18 years will be recruited from five community pharmacies and assigned to equally sized groups to receive either pharmacist-led education interventions or usual care with no intervention. A total of 400 (control = 200, study = 200) patients will be included, with prescriptions comprised of antibiotics for LRTIs. The outcomes measured in both groups will be a combination of treatment cure rate and adherence, which will be assessed using the Morisky Medication Adherence Scale and pill count. The trial comprises pharmacist-led educational interventions to improve treatment outcomes for patients with LRTIs. This study might establish the groundwork for pharmaceutical care of LRTIs patients with antibacterial therapy and the future delivery of a care strategy for the improvement of LRTIs treatment outcomes in post-conflict, remote areas of the third world and LMICs.

**Trial registration**: Chinese Clinical Trials Registry, identifier: ChiCTR2000040453, registered on 28 November 2020.

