### 2.2. Study Design

This is a two-arm, single-blind, individual, randomized, controlled trial that will determine the effectiveness of pharmacist-led educational interventions for the patients who approached pharmacies with LRTI prescriptions. The present study will be conducted in a community-pharmacy setting in the rural region of Pakistan. The iRCT will be favored to reduce possible contamination between the two groups. The standard protocol items; recommendation for interventional trials (SPIRIT) used in the current trials are presented in Figure 1 and the checklist (Additional File S1).

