### 2.4. Data Collector’s Eligibility Criteria and Training

The data collector team will be comprised of healthcare workers (pharmacists, LHWs, and vaccinators). The trained pharmacists will select pharmacies (5 = control, 5 = interventional) to recruit participants, with their full consent (Additional File S2). Leaflets and materials related to the appropriate use of antibiotics will be provided to the participants at the pharmacies.

The data collector team will have the required qualifications, and the pharmacist must be registered with Pakistan Pharmacy Council (PPC) [29]. The pharmacist’s abilities are directly related to the quality of the study, which depends solely on the pharmacist’s competency. Consequently, the pharmacists involved in this study will have experience in previous patient-centered care services at community pharmacies or be engaged with population-based studies.

The pharmacists and other healthcare members must be trained for the counseling sessions with participants at community pharmacies. Effective training in communication skills will be held before the execution of the trials, and pseudo-patient training will be arranged to assess their counseling skills at community pharmacies. Finally, the principal investigator will approve the trained team for the trial.

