### 2.10. Concealment of Allocation

Before preceding to random allocation into either the control or intervention arm of the study, an informed consent/agreement ascertainment and eligibility will be obtained. The allocation will not be known to research assistants, participants, or trial representatives (pharmacists) until the point of randomization. Interventional households will only be known to research assistants. The participants will be introduced to the interventional arm facilitator individually, by mobile phone call. If the pharmacists and research teams are allocated to the control arm, they will continue to regularly contact the allocated UC.

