### 2.17. Statistical Analysis Methods

According to the Consolidated Standards of Reporting Trials (CONSORT) for RCTs, all the findings will be reported as per the given guidelines [41]. Data will be analyzed through IBM-SPSS-Statistics (version 21) and STATA (version 11). The basis of primary analysis is to educate the population with LRTIs, and the secondary analysis will be based on the adherence rate and behavior of the population. For the primary endpoint analysis, a linear mixed model will be employed. The mixed model will include the visits, interactions with the treatment group, and baseline measurement of BMQ and PAS-QA as covariates, and subjects as a random effect. The mean differences (MD) between the two arms at each visit, with a confidence interval (CI 95%), will be derived from a generalized mixed model, along with each visit from the treatment arm. Before unmasking the trial, all analyses will be defined in detail with their assigned statistical plans.

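### The protocol contradicts itself on the unit of allocation; if pharmacists or pharmacies carry the arm, the sample size and the subject-only model ignore the clustering

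*Protocol article*

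**What the plan says.** Four statements bear on what is allocated.

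- Section 2.2: "This is a two-arm, single-blind, individual, randomized, controlled trial". It gives reduced contamination between the groups as the reason for individual randomisation.
- Section 2.9, patient level: "For every participant that is recruited, a sample 1:1 is used to allocate them into control and interventional groups". Pharmacist level, in the next sentence: "Finally, ten pharmacists will be randomized to the intervention and control arms 1:1 and the permuted method will be used".
- Section 2.4, pharmacy level: "The trained pharmacists will select pharmacies (5 = control, 5 = interventional) to recruit participants".
- Abstract: "Patients aged > 18 years will be recruited from five community pharmacies".

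Section 2.10 promises concealment: "The allocation will not be known to research assistants, participants, or trial representatives (pharmacists) until the point of randomization". It places randomisation after consent and the eligibility check, yet it also speaks of pharmacists who are allocated to the control arm.

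Section 2.7 states 80% power, 5% alpha, 20% attrition and 400 patients (200 per group). It gives no effect size, standard deviation, ICC or design effect. The primary model in section 2.17 has visit, its interaction with treatment group, "baseline measurement of BMQ and PAS-QA as covariates, and subjects as a random effect". No pharmacy or pharmacist term is named.

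**The concern.** The unit of allocation decides the sample size formula, the error term of the primary comparison and whether concealment is possible. Here a reader cannot tell whether a patient's arm comes from a patient-level list, from the pharmacist who serves them, or from the pharmacy they walk into.

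The intervention is counselling, and section 2.4 itself ties study quality to the competence of the pharmacist. Outcomes of patients who share a pharmacist or pharmacy are therefore likely to be correlated. If the arm goes with the pharmacist or pharmacy, the treatment comparison rests on five units against five. A random effect for subjects handles repeated visits of one patient, but not patients who share a deliverer. A chance difference between two sets of five pharmacies could then pass for an intervention effect. If pharmacies are labelled by arm in advance, staff also know the arm before consent and could recruit selectively, which no analysis repairs.

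**Working it through.** **1. The plan's own figure.** The 400 cannot be reproduced as a two-arm power calculation, because no effect is stated. The one complete set of inputs in section 2.7 (95% confidence, 5% margin) gives 1.96² × 0.25 / 0.05² = 384.1, so 385 before attrition and 385 / 0.8 = 482 after it. Read backwards, 200 × 0.8 = 160 completers per arm. The effect detectable with 80% power (two-sided 5%, independent patients) is then (1.960 + 0.842) × √(2/160) = 0.313 SD. This effect is back-solved and is not in the protocol. It serves only to set power at 80% under independence.

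**2. Full clustering (pharmacist or pharmacy carries the arm).** Inputs: ten clusters (sections 2.4 and 2.9), 320 completers, hence m = 320 / 10 = 32 per cluster. The ICC is assumed.

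- Design effect: DE = 1 + (32 − 1) × ICC
- Noncentrality: 0.313 / √(2 × DE / 160) = 2.80 / √DE
- Power: normal reference, or noncentral t with 10 − 2 = 8 df
- Type I error of a model that ignores clusters: 2 × [1 − Φ(1.96 / √DE)]

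| ICC | DE | Correct SE / model SE (√DE) | Effective n per arm (160/DE) | Power, normal | Power, t 8 df | Type I error |
|---|---|---|---|---|---|---|
| 0 | 1.00 | 1.00 | 160 | 80% | 69% | 5% |
| 0.01 | 1.31 | 1.14 | 122 | 69% | 58% | 9% |
| 0.02 | 1.62 | 1.27 | 99 | 60% | 49% | 12% |
| 0.05 | 2.55 | 1.60 | 63 | 42% | 34% | 22% |
| 0.10 | 4.10 | 2.02 | 39 | 28% | 23% | 33% |

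The first row separates two losses. Moving to 8 df costs about 11 points even at ICC 0. The rest comes from the design effect.

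**3. Patients individually randomised, clustering by deliverer in the intervention arm only.** The variance of the difference is inflated by the average (1 + DE) / 2 = 1.16 / 1.31 / 1.78 / 2.55 for ICC 0.01 / 0.02 / 0.05 / 0.10. The same type I formula gives about 7% / 9% / 14% / 22%.

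**4. Every pharmacist serves both arms.** Pharmacist differences then largely cancel in the treatment contrast, and the inflation largely falls away. The 1:1 pharmacist randomisation in 2.9 and the five/five split in 2.4 do not describe this arrangement.

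**5. Number of pharmacies.** The abstract's five cannot be the ten of section 2.4. If five pharmacies carried the arm they could not be split equally, and clusters would average 320 / 5 = 64 completers, so the loss would be larger than in step 2.

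**The case against.** A reader might infer that the stated 80% power and 5% alpha are simply not delivered. The protocol does not support so flat a statement. The result needs arm-specific pharmacists or pharmacies and an ICC above 0. With no stated effect the 80% cannot be checked at all, and the gain from adjusting for baseline is not counted in the figures.

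The statements can also be partly reconciled. Ten pharmacists split 1:1 and ten pharmacies split five and five may be one scheme. Patients could be randomised individually and then routed to an arm-specific deliverer: section 2.9 has pharmacists notified once the participant has agreed, and section 2.10 has participants introduced by telephone to the facilitator of the intervention arm. On that reading differences between pharmacy catchments are balanced across arms and only deliverer effects remain, which may be weak under usual care. A reader might infer that this causes as much clustering as randomising pharmacies, but step 3 shows a smaller inflation if only the intervention arm clusters. Nor would concealment fail on that reading. It fails only if pharmacies are labelled by arm in advance, as section 2.4 suggests.

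All of this stands as a limit on the size of the problem. It does not remove the contradiction, and the routing reading still leaves patients nested in arm-specific pharmacists whom the model in 2.17 ignores. A later analysis plan could add a model term, but it cannot decide after recruitment what was randomised.

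**Conclusion.** The contradiction about the unit of allocation and the number of pharmacies is in the text and is certain. The statistical consequence is conditional. Where pharmacists or pharmacies carry the arm, following section 2.17 as written gives intervals that are too narrow for any ICC above 0, by a factor of 1.14 to 2.02 over the assumed ICC range of 0.01 to 0.10 with full clustering. Power and error rates across the readings are those in the working. They rest on equal clusters, an assumed ICC, 20% attrition exactly as planned and a back-solved effect, so they show what is at stake and do not estimate this trial's power. The unit must be fixed before recruitment, because concealment and the error term both depend on it.

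**What to change.** State one unit of allocation, and reconcile the abstract and sections 2.2, 2.4, 2.9 and 2.10 with it, including the number of pharmacies. There are two coherent options.

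(a) **Keep individual randomisation.** Delete the randomisation of pharmacists in 2.9 and the five/five pharmacy split in 2.4. Randomise after consent in permuted blocks stratified by pharmacy, with every pharmacy recruiting to both arms. Add pharmacy to the model in 2.17, and a random intercept for the delivering pharmacist if deliverers are arm-specific. Correct the rationale in 2.2: patients of both arms sharing a pharmacy raises contamination. Name this as the downside of the option and say how it will be handled. Cost: amendment wording and one or two model terms, with no extra patients.

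(b) **Call it a cluster trial.** The biostatistician, not the pharmacists, allocates the pharmacies. Add a pharmacy random intercept with small-sample degrees of freedom (Kenward-Roger, or 8 df with ten pharmacies). Restate the power in 2.7 with an assumed ICC and the design effect, and revise 2.10 to say how patients are recruited when the pharmacy's arm is known. Cost: the stated power falls at 400 patients. Keeping 80% with ten pharmacies needs m = 160 × (1 − ICC) / (5 − 160 × ICC) completers per pharmacy (normal approximation, so optimistic with 8 df). At ICC 0.01 this is 47, or 470 / 0.8 = 588 enrolled; at ICC 0.02 it is 88, or 880 / 0.8 = 1,100. From ICC 5 / 160 = 0.03125 upwards no number of patients is enough and more pharmacies are needed.
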